### Study duration

The study duration is a 6-month study period from 1 December 2021 to 31 May 2022. During this period, all participants will be followed up for a period of 7 days post-surgery. At the end of this trial, the result will be published in a peer-reviewed journal, and deidentified data set will be publically available to other researchers on a permanent web link that will be provided by a peer-reviewed journal.

### Trial status

The first case was recruited on 2 December 2021, and as of 7 April 2022, 45 patients were registered out of the required sample size of 58 for this protocol version 3 as of 21 May 2022.

#### Ethical considerations

This clinical trial has been approved by the Kampala International University Research Ethics Committee (KIU-REC) under the number KIU-REC-2021-24. The standard official consent form for the Kampala International University Research and ethical review committee will be adopted. Respective hospital surgical consent forms conforming to WHO consenting information standards will be used, and oral translation to the local language will be done by the researcher or his delegated assistant. Participant recruitment will be done non-discriminatively regardless of race, color, or tribe. All those who meet the selection criteria will have equal chances of participating. The inclusion and exclusion criteria will be followed strictly. The trial will be overseen by the Institutional Research Ethics Committee (IREC) of Kampala International University.

### Adverse events

There are minor discomforts anticipated in this study: pain associated with venipuncture during the process of blood collection for investigations which will be necessary as routine patient preparation for surgery. Patients are then expected to undergo pain and stress of hemorrhoids operation and bleeding after the operation. These discomforts are not imposed by the study but rather expected routine from patients who undergo such operations.

### Ancillary and post-trial care

The outcome of the study may indirectly help participants to obtain care during study time and will be recognized during publications. Diverse outcomes, e.g., too much pain, will result in converting from local to SA (crossover) and getting other analgesics other than those prescribed in the trial.

### Trial discontinuation

The trial will be discontinued for individual patients due to non-adherence, e.g., not completing the specified duration of follow-up, diverse outcomes, e.g., too much pain resulting in converting from local to GA (cross over) and getting other analgesics other than those prescribed in the trial.

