According to a similar randomized control trial that compared open hemorrhoidectomy under local anesthesia versus supine anesthesia at the Korle Bu Teaching Hospital in Ghana [16], the difference in the mean pain scores between the 2 groups was *δ* = 0.73; pooled standard deviation in the mean pain scores *S* = 1.9 (average of 2.356 for local anesthesia and 1.479 for supine anesthesia), an estimated sample size of 104 participants per group, was obtained. Since at the time of the proposed study, nothing was known about the mean pain score following OH under local anesthesia and the real difference in clinical outcome between the two techniques in Uganda, the sample size was adjusted using Slovin’s formula as detailed by Ellen [17] based on the hospital records, Kampala International University Teaching Hospital which registered an average of 33 cases of grade 3 or 4 hemorrhoids in a period of 6 months that corresponded to the intended data collection period; thus, a sample size of 26 participants per group was obtained which was increased to 29 participants in each arm, based on a rate of 10% in each arm to compensate for the loss to follow-up and non-responsiveness found.

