### Study variables

#### Primary outcome variable

The occurrence of pain following open hemorrhoidectomy will be determined in both groups using the area under the curve (AUC) for visual analog scale (VAS). The VAS will be used in an interval of 2, 4, and 6 h and 7 days postoperatively (the lower end of the scale labeled “0” means no pain while the upper end of the scale “10” signifies the worst imaginable pain).

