### Data processing and analysis plan

Data will be statistically analyzed using IBM Statistics SPSS for Windows 23.0. The primary outcome will analyze all randomized patients (on an intent-to-treat (ITT) basis) and per-protocol (PP) population. The mean pain scores at rest and their standard deviations will be computed and compared using one-way ANOVA tests. VAS will be stratified as ordinal (0 as no pain, 1–3 as mild, 4–6 as moderate, and 7–10 as severe); the significance of the difference in the mean scores between local and saddle groups will be determined by the Kruskall-Wallis (*H*) test at 95% confidence interval, regarding *p* < 0.05 as statistically significant; furthermore, the mean pain scores will be analyzed for significant differences in the area under the curve (AUC) for VAS (2-sample *t*-test). The mean operative time and standard deviation will be computed for each technique of open hemorrhoidectomy. Cross tabulation will be performed between the two open hemorrhoidectomy techniques for categorical cost-effective analysis. The difference in the means will be compared using the *t*-test and their corresponding two-tailed p-value, regarding *p* < 0.05 as statistically significant.

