### Unblinding

The recommendation to withdraw a patient from the trial will be decided by the principal investigator in case of failure of the anesthetic technique and loss of follow-up. In addition to that, outcome assessors will be blinded, and the criterion for unblinding is if they observe adverse effects related to intervention that needs to be disclosed to the attending clinician.

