### Missing data

Missing data will be reported as missing during the analysis. Clinical characteristics of those lost to follow-up and crossovers will be compared to those retained in both groups.

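### Lost or incomplete follow-up is treated as withdrawal and left missing, so a patient with no day-7 pain score has no primary AUC, although the plan promises to analyze all randomized patients

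*Protocol article*

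**What the plan says.** Protocol article, by section:

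- **Trial discontinuation:** "The trial will be discontinued for individual patients due to non-adherence, e.g., not completing the specified duration of follow-up". Conversion of the anesthetic and use of non-trial analgesics are listed there too; this point does not concern them.
- **Unblinding**, with the same sentence under **Interim analysis:** withdrawal of a patient is "decided by the principal investigator in case of failure of the anesthetic technique and loss of follow-up".
- **Missing data:** "Missing data will be reported as missing during the analysis". The section then adds: "Clinical characteristics of those lost to follow-up and crossovers will be compared to those retained in both groups".
- **Data processing and analysis plan:** "The primary outcome will analyze all randomized patients (on an intent-to-treat (ITT) basis) and per-protocol (PP) population". The AUC for VAS is compared by a two-sample t-test.
- **Primary outcome variable:** pain is summarized as an AUC of the VAS, and "The VAS will be used in an interval of 2, 4, and 6 h and 7 days postoperatively".
- **Participant recruitment and study procedure:** patients who cannot return on day 7 are to be interviewed by telephone.
- **Sample size determination:** 26 per group was raised to 29, "based on a rate of 10% in each arm to compensate for the loss to follow-up and non-responsiveness found".

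**The concern.** Failing to reach a patient on day 7 produces a missing value. The protocol gives it a second meaning: the patient is discontinued or withdrawn. Three sections say so, while the analysis plan says that every randomized patient is analyzed. A reader cannot tell whether such a patient belongs to the intention-to-treat set.

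The choice of endpoint makes this matter. An AUC that runs to day 7 needs a day-7 score. If that score is absent and stays absent, the t-test can use only patients with all readings, whatever the population is called. The result is then a comparison of patients who could be reached at day 7. If being reached depends on pain after discharge, and does so differently by arm, the comparison is biased. Comparing the characteristics of the lost with the retained would describe that problem without correcting it.

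A secondary point is that the principal investigator, who gives the local infiltration and operates, also decides on withdrawal. Only patients and outcome assessors are blinded. Loss to follow-up does not need to be a decision by someone who knows the arm.

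**Working it through.** **1. The plan's own figure.** The allowance reproduces: 26 / (1 − 0.10) = 28.9, rounded up to 29 per arm, 58 in total. (26 × 1.10 = 28.6 also rounds to 29.) Raising 26 to 29 treats about three patients per arm as not evaluable.

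**2. Patients involved.**

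| Share with no day-7 score | Of 29 per arm | Of 58 |
|---|---|---|
| 5% (assumed) | 1.5 | 2.9 |
| 10% (the whole allowance) | 2.9 | 5.8 |
| 20% (assumed) | 5.8 | 11.6 |

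At 10%, 29 × 0.90 = 26.1 patients per arm remain.

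**3. Why the AUC fails without day 7.** The protocol names no AUC rule; the trapezoid rule is assumed here, with day 7 at 168 h. The span is 168 − 2 = 166 h. Each reading's weight is half the distance between its neighbors (for an end reading, half the distance to its one neighbor):

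| Reading | Weight (h) | Share |
|---|---|---|
| 2 h | (4 − 2)/2 = 1 | 0.6% |
| 4 h | (6 − 2)/2 = 2 | 1.2% |
| 6 h | (168 − 4)/2 = 82 | 49.4% |
| Day 7 | (168 − 6)/2 = 81 | 48.8% |

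Of the 166 hours, 162 (97.6%) lie between 6 h and day 7. Without a day-7 score and without imputation, the AUC over the stated period cannot be computed, even when the other three readings are complete.

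**4. Precision.** Going from 29 to 26 per arm multiplies the standard error by √(29/26) = 1.056. But 26 is the number the plan arrived at before adding the allowance, so this is a return to planned precision.

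**5. Possible bias.** If m of 29 patients in an arm are lost, the complete-case mean differs from the full-arm mean by (m/29) × (mean of retained − mean of lost). With m = 3, 3/29 = 0.103. Each VAS point of gap in time-averaged pain therefore moves that arm's mean by about 0.10. Assumed gaps of 1 to 3 points give 0.10 to 0.31. The shift cancels between arms only if it is equal in both. The documents give no information on the gap.

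**The case against.** The strongest reply has five parts.

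- **No section orders early scores to be removed.** This is correct. A reader might infer that the protocol throws away the 2, 4 and 6 h scores, but the text does not say so. Their absence from the AUC test follows only from the endpoint definition, the t-test and the missing-data rule together. The separate comparisons of mean scores and of ordinal pain categories could still use them.
- **A missed visit is not a missed score.** Also correct. The telephone interview covers patients who cannot come back, so only those reached by neither route are affected. It lowers the number but does not settle what happens to them.
- **The 10% is not a forecast of missing day-7 scores.** It covers non-responsiveness as well, so 6 of 58 is an upper planning figure. Nor should the 5.6% larger standard error be read as a loss against plan.
- **Day 7 is the last contact, so the discontinuation label loses no later reading, and deleting it gives nobody an AUC.** True, which is why wording alone is not enough. The label still contradicts the intention-to-treat statement.
- **Handling of a missing reading belongs in a statistical analysis plan.** That would answer silence. Here the protocol states rules on withdrawal and missing values, and those rules conflict with its own analysis population.

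It is also fair to say that a mixed model may add little precision. The 2 h and 4 h readings together carry about 1.8% of the weight, so most of what can be recovered depends on how strongly the 6 h and day-7 scores correlate, which the documents do not give.

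**Conclusion.** The concern holds in a limited form. The sections on discontinuation, interim analysis and unblinding conflict with the promise to analyze all randomized patients, and the stated primary test becomes a complete-case analysis for want of day-7 scores. It affects up to about 3 of 29 per arm (6 of 58) if the whole 10% allowance is missing day-7 data, and about 3 of 58 at an assumed 5%. The main consequence is possible bias, whose size and direction cannot be determined from the protocol.

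This rests on two readings: that the AUC spans all four listed times, and that reporting data as missing means no imputation. The weights also assume the trapezoid rule.

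**What to change.** 1. Reconcile Trial discontinuation, Interim analysis and Unblinding with the analysis plan: incomplete or lost follow-up is recorded as missing data and is not a ground for discontinuing or withdrawing a patient. The other listed grounds are outside this point.
2. State that every VAS score collected stays in the intention-to-treat set under the randomized arm.
3. Estimate the primary between-arm difference from a repeated-measures mixed model with arm, time and their interaction, using all available scores. Take the contrast with the AUC weights. Under the trapezoid rule this is 1·d(2 h) + 2·d(4 h) + 82·d(6 h) + 81·d(day 7), where d is the arm difference at each time; dividing by 166 gives time-averaged VAS. The estimand is then still the AUC difference; an unweighted average of the four times would be a different quantity.
4. Keep the complete-case AUC t-test as a sensitivity analysis.

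**Cost.** Wording and analysis only, with no added visits or patients; the named software can fit the model. The model assumes day-7 scores are missing at random given arm and earlier scores, which is weaker than the complete-case assumption but cannot be checked. The gain in precision may be small. Because outcomes were examined at the interim analysis on 10 March 2022 and 45 of 58 patients were registered by 7 April 2022, the change should be dated and documented as an amendment, with its timing relative to that analysis stated.

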### Randomization and blinding

After fulfilling the enrollment criteria and obtaining the informed consent, the participants will be allocated randomly by assistant researchers well trained to either the local anesthesia group (group A) or the saddle block group (group B) by using envelope allocation concealment whereby half of the envelopes will contain a chit with letter A while the other half will have a chit with letter B signifying local anesthesia and saddle block, respectively. The content of the envelope will be opened once the patient is in the theater, and the patients and outcome assessors will be blinded about the anesthesia.

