#### Participant recruitment and study procedure

Participants will be recruited from surgical outpatient by trained research assistants. Patients with uncomplicated 3rd- or 4th-degree hemorrhoids will be assessed for study eligibility using a screening log. Written informed consent will be obtained from the eligible participants.

The patients admitted for elective hemorrhoidectomy will undergo pre-anesthetic evaluation the day before surgery and will be given fasting guidelines including 6 h for solid foods and 2 h to anesthesia for clear fluids like water. All patients will receive prophylactic antibiotics (intravenous 500 mg of metronidazole) within 60 min prior to incision [18]. Two hours before surgery, the patient will be receiving an enema intrarectal. All patients scheduled for surgery will be informed and admitted a day prior to surgery, prepared, and included in the theater program in order to maintain continuity of care.

Once in the operating room, vital signs will be taken (blood pressure, pulse rate, oxygen saturation, and monitoring of the ECG). Co-loading of intravenous crystalloids, namely normal saline and or ringers’ lactate, will be done using a restrictive approach of fluid administration and undergo open hemorrhoidectomy under saddle block [19].

Aseptic protocols will be observed for all groups. Group A patients, in lithotomy or prone jack-knife positions, will be infiltrated with bupivacaine 0.5% at a maximum safe dose of 2 mg/kg with adrenaline (1:200,000) following the technique of Jinjil et al. [20]. The local anesthetic mixture will be administered by the principal investigator as follows: The first two injections will be applied bilaterally (1 and 4), 5 mm from the border of the perianal skin, and the mixture will be injected at 12 and 6 o’clock (3 ml each side). Thereafter, further 4 injections will be administered into 4 quadrants performing a diamond shape (2, 3, 5, and 6), 5 mm from the anal opening; every 1 ml will be injected at a 4-cm, 3-cm, and 2-cm depth from the skin, respectively, as shown in Fig. 1.

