### Interim analysis

Biostatisticians will perform an interim analysis once we register a total of 36 patients for open hemorrhoidectomy using the two different anesthetic techniques, which is 62.1% of the planned number of patients. The primary, secondary, and tertiary outcomes will be evaluated to compare open hemorrhoidectomy using local anesthesia versus saddle block among patients with primary uncomplicated 3rd- and 4th-degree hemorrhoids.

The Data Monitoring Committee would recommend continuing, discontinuing, or modifying the trial, if concerns regarding the effect and safety of the participants will arise.

The recommendation to withdraw a patient from the trial will be decided by the principal investigator in case of failure of the anesthetic technique and loss of follow-up.

A recommendation of trial termination would be considered by the principal investigator, clinical trial institution, and ethics committee if achieving the difference in treatment effects is unlikely or if intolerable adverse effects occurred. The detailed results remain confidential to the investigator. The interim analysis was done on 10 March 2022, and continued recruitment was recommended.

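### Withdrawal rules remove randomized patients for failed anesthesia or pain-driven conversion, which contradicts the promised ITT analysis and can bias the pain comparison by an unknown amount

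*Protocol article*

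**What the plan says.** The Data processing and analysis plan section states: "The primary outcome will analyze all randomized patients (on an intent-to-treat (ITT) basis) and per-protocol (PP) population".

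Other sections of the protocol article take randomized patients out:

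- **Trial discontinuation** ends the trial for individual patients for non-adherence and for adverse outcomes, with this example: "too much pain resulting in converting from local to GA (cross over) and getting other analgesics other than those prescribed in the trial".
- **Interim analysis**: "The recommendation to withdraw a patient from the trial will be decided by the principal investigator in case of failure of the anesthetic technique". **Unblinding** repeats the rule: "decided by the principal investigator in case of failure of the anesthetic technique and loss of follow-up".
- **Exclusion criteria** list failure of the anesthetic technique beside baseline conditions.
- **Missing data** reports missing values as missing and adds: "Clinical characteristics of those lost to follow-up and crossovers will be compared to those retained in both groups".

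On timing, Randomization and blinding says: "The content of the envelope will be opened once the patient is in the theater". On who decides, Participant recruitment and study procedure says "The local anesthetic mixture will be administered by the principal investigator as follows", and the same person performs the hemorrhoidectomy.

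Ancillary and post-trial care describes the pain-driven conversion differently. There, too much pain "will result in converting from local to SA (crossover) and getting other analgesics other than those prescribed in the trial", with no mention of leaving the trial.

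**The concern.** The primary outcome is postoperative pain (AUC of the VAS at 2, 4 and 6 h and day 7), and one trigger for removal is pain. Patients would therefore be lost on an event that may predict the endpoint. The decision on failed technique rests with someone who knows the arm.

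The loss may also differ between arms. The only conversion example starts from local anesthesia, although the Introduction names failed block as a saddle block complication, so both arms can be affected.

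If conversion goes with worse later pain and is commoner under local anesthesia, the local mean is understated. If local anesthesia is truly more painful, the arms then look more alike than they are. That matters in a trial labelled an equivalence trial, whose hypothesis is no significant difference.

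**Working it through.** **1. Do the rules act after randomization?** The envelope is opened in theater, after eligibility and consent. Failure of the allocated technique, and conversion from it, can be seen only after that. They are removals after randomization, not eligibility decisions.

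**2. Can the rules be squared with ITT?** The anesthetic is given once, so little study treatment is left to stop when it fails. The Interim analysis and Unblinding sections speak of withdrawal from the trial, Trial discontinuation puts conversion beside incomplete follow-up, and Missing data sets crossovers against patients retained. No section says that VAS readings continue after conversion or withdrawal.

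**3. How large could the effect be?** The plan gives no figure to reproduce here: no conversion or failure rate, no link between conversion and VAS, and no SD for the AUC. What follows is a sensitivity calculation.

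Inputs from Sample size determination:
- 29 per arm, which is 26 plus the loss allowance, so 29 − 26 = 3 losses is a convenient case
- SD 2.356 for local anesthesia; 1.479 for the comparator, used here for saddle block
- 0.73 VAS points, used there as the margin

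Assumptions: normal scores at a single reading, and k patients removed on a variable with correlation r to their VAS.

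Formula: shift in an arm's mean = r × d(k) × SD. Here d(k) is the fall in the mean of 29 standard normal scores when the k largest are removed. Simulation with 200,000 samples gives d(1) = 0.0727 and d(3) = 0.1915.

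- Local arm, k = 3, r = 1: 0.1915 × 2.356 = 0.451
- Local arm, k = 1, r = 1: 0.0727 × 2.356 = 0.171
- Saddle block arm, k = 3, r = 1: 0.1915 × 1.479 = 0.283
- Saddle block arm, k = 1, r = 1: 0.0727 × 1.479 = 0.108

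Net shift = local shift − saddle block shift. A positive value means that local anesthesia looks better than it is.

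| Lost: local / saddle block | r = 0 | r = 0.5 | r = 1 | r = 1 as share of 0.73 |
|---|---|---|---|---|
| 1 / 0 | 0 | 0.09 | 0.17 | 23% |
| 3 / 0 | 0 | 0.23 | 0.45 | 62% |
| 3 / 1 | 0 | 0.17 | 0.34 | 47% |
| 3 / 3 | 0 | 0.08 | 0.17 | 23% |
| 1 / 3 | 0 | −0.06 | −0.11 | −15% |

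The r = 1 column is a worst case. A negative r reverses the signs: 3 / 0 at r = −0.5 gives −0.23.

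**4. Cross-check by another route.** Shift = (share removed) × (removed mean − retained mean). If three of 29 are removed and their VAS is an assumed 2 to 5 points above the rest, the shift is 3/29 × 2 = 0.21 to 3/29 × 5 = 0.52. This is the same order.

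**5. Against the trial's precision.** SE of the difference = √((2.356² + 1.479²)/29) = √(7.738/29) = 0.52, so the 95% half-width is 1.96 × 0.5166 = 1.01. The 0.23 shift is 0.44 SE and the 0.45 shift is 0.87 SE.

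**The case against.** The best defense is that the plan already names both ITT and per-protocol sets. Removal for failure, conversion or other analgesics is what a per-protocol definition contains, and the rest could sit in a full protocol or SAP that is not shown. No sentence says that VAS collection stops at conversion. This makes the loss of scores a consequence of following the text, not a demonstrated fact. It does not remove the conflict: the article itself fixes withdrawal from the trial, and does not limit it to the per-protocol set.

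Failed technique in the exclusion criteria could mean a past failure. That is possible, but the other three sections carry the point without it. The Interim analysis and Unblinding sections do speak only of a recommendation, and the same clause covers loss to follow-up.

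With a half-width of 1.01, no interval could lie within ±0.73 at these SDs, and the analysis section contains no margin test. This is correct, so the percentages of 0.73 are a yardstick and not a decision rule. The damage would come through the planned difference tests, where a shift toward zero makes a wrong finding of no difference more likely. Low power contributes to that separately.

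Converted patients receive another anesthetic and extra analgesia, so their early VAS could be lower than that of the others. This too is correct, and it is why the direction is left open.

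Keeping converted patients in the local arm can dilute a true difference, particularly if they convert to spinal anesthesia. The planned per-protocol analysis beside ITT addresses this.

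**Conclusion.** The concern holds. The withdrawal rules contradict the ITT commitment, and they bear on the primary outcome through an event related to pain. Neither the size nor the direction of any bias can be established from the document. Under the assumptions above, three losses in the local arm alone shift its mean by 0 to 0.45 VAS points for correlations from 0 to 1. The shift is smaller when losses are balanced, and reverses when saddle block losses dominate or the correlation is negative. These figures refer to one VAS reading, not the AUC. The text should be corrected. Confidence is medium, because actual conversions may be few and readings may in practice have continued.

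**What to change.** - In Trial discontinuation, Interim analysis and Unblinding, state that pain, conversion, other analgesics or failed technique end only the allocated technique, under one rule for both arms.
- Delete failed technique from the exclusion criteria.
- Keep every randomized patient in VAS follow-up at 2, 4 and 6 h and day 7, and in the ITT set as randomized. Conversions leave only the per-protocol set.
- Name one conversion technique in Ancillary and post-trial care and Trial discontinuation, which now give SA and GA respectively.
- For patients already enrolled, report these exclusions and discontinuations by arm and include any VAS scores recorded.

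The cost is wording in five sections. The VAS readings and the day 7 visit or telephone call are already planned, and the sample size stays at 29 per arm. Timing limits the gain: 45 of 58 patients were registered by 7 April 2022, so the follow-up change reaches at most 58 − 45 = 13, and probably fewer by the version date of 21 May 2022. The ITT definition and the by-arm report can still cover all 58, but readings never taken cannot be recovered.
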